### Follow-up

After the completion of 12 sessions of acupuncture, we will follow patients via telephone or WeChat to score the HAMA, GAD-7, and PSQI scores in the first month and the third month to determine whether the efficacy can be maintained.

### Data monitoring and analysis

Data will be saved on paper as recorded by the assessors. All original data will be stored in the medical record room of the First Affiliated Hospital of Guangzhou University of Chinese Medicine for 3 years. An independent assistant will monitor the process of collecting data and the Ethics Committee of the First Affiliated Hospital of Guangzhou University of Chinese Medicine will carry out audits at regular intervals.

Two independent study assistants will input the data, check by themselves whether the input data have discrepancies, and correct them. IBM SPSS Statistics version 26 (IBM SPSS Inc., Chicago, USA) will be used to analyze the data. The HAMA, GAD-7, and PSQI scores assessed in each group will be subjected to normality tests. If the scores obey a normal distribution, a one-way analysis of variance will be performed. If not, the Kruskal-Wallis rank sum test will be performed. The repeatedly assessed HAMA, GAD-7, and PSQI scores in the MA or PA group will be subjected to a normality test. If the scores obey a normal distribution, repeated measurement analysis of variance will be performed. If not, the Friedman rank sum test will be performed. If the significance of the *F*-test of the univariate linear model is greater than 0.05, CORT and ACTH will be subjected to covariance analysis. If not, the Kruskal-Wallis rank sum test will be performed.

All statistical tests will be two-sided, and the significance level will be set at 0.05. If the patient drops out, we will follow the intention-to-treat (ITT) and use the last score or serological indices assessed as the final score or indices.

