Therefore, we designed a randomized controlled trial that focus on the efficacy of manual acupuncture (MA) versus placebo acupuncture (PA) on GAD in perimenopausal women. To evaluate the therapeutic efficacy of GAD, the primary outcome measure used in our protocol is the change in scores on the Hamilton Anxiety Scale (HAMA). The secondary outcome measures are the changes in scores on the Generalized Anxiety Disorder Scale (GAD-7) and Pittsburgh Sleep Quality Index (PQSI), and laboratory indicators related to the current possible pathogenesis of GAD, mainly including CORT and ACTH. This protocol aims to explore the efficacy of MA in GAD patients who would not prefer drug or CBT therapies. Meanwhile, we hope to explore the possible mechanism of acupuncture on GAD by measuring the levels of CORT and ACTH in serum.

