### Sample size

According to preliminary trials [20, 21], we chose the HAMA score as the outcome to calculate the sample size. After treatment, the HAMA score of MA was 14.0±3.2, and the HAMA score of PA was 19.4±5.3. PASS version 15.0 (NCSS, LLC. Kaysville, UT, USA) was used to estimate the sample size with a power level of 90% and a two-sided significance level of 5%. After calculation, we set the sample size of 44 patients in each group to observe the significant difference between the two groups. With a 20% withdrawal rate, we plan to enroll a total of 112 patients with 56 patients in each group.

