### Primary outcome

#### HAMA score

The primary outcome of this study is the HAMA [25] score, which measures the severity of anxiety. The HAMA is a 14-item scale rated on a 4-point scale with a total score ranging from 0 to 56. A higher score means a higher range of anxiety. According to studies, a score higher than 28 indicates severe anxiety, a score between 28 and 21 indicates moderate anxiety, a score between 20 and 14 indicates mild anxiety, and a score lower than 14 indicates no anxiety. HAMA will be assessed on the first day, the 14th day, and the 28th day of the trial.

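### The between-arm HAMA test is unadjusted and tied to no visit; one baseline-adjusted day-28 contrast should be named as primary

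*Protocol article*

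**What the plan says.** In the protocol article, under Data monitoring and analysis, HAMA, GAD-7 and PSQI scores are first tested for normality. Then: "If the scores obey a normal distribution, a one-way analysis of variance will be performed"; otherwise Kruskal-Wallis is used. No visit and no covariate is named. A second step follows: "The repeatedly assessed HAMA, GAD-7, and PSQI scores in the MA or PA group will be subjected to a normality test". It leads to repeated-measures ANOVA or, failing normality, to Friedman. The same paragraph reserves covariance analysis for CORT and ACTH. On error control it says only: "All statistical tests will be two-sided, and the significance level will be set at 0.05".

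The primary outcome is described in two ways. The Background says that "the primary outcome measure used in our protocol is the change in scores on the Hamilton Anxiety Scale (HAMA"). The HAMA score section under Primary outcome names the score itself and gives the visits: "HAMA will be assessed on the first day, the 14th day, and the 28th day of the trial". The Follow-up section adds HAMA at one and three months after treatment. No visit is called primary. The Sample size section, however, works from a single time point: "After treatment, the HAMA score of MA was 14.0±3.2, and the HAMA score of PA was 19.4±5.3".

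**The concern.** The trial asks whether MA beats PA on HAMA. A reader should be able to point to one number that answers this, and the article does not settle which one.

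- **Visit and form of outcome.** The between-arm test could be run at any of four post-baseline visits, on raw or change scores. If more than one visit can carry the claim, the false-positive rate exceeds 5%.
- **Baseline.** HAMA is measured in everyone on day 1, yet the stated model does not adjust for it. Precision is lost, and a chance imbalance at baseline is not corrected in the estimate.
- **Within-arm step.** Entry requires HAMA between 14 and 28, so some fall from regression to the mean is plausible in both arms. A significant fall in one arm and not in the other is not evidence that the arms differ.

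**Working it through.** **Inputs from the article.** Means 14.0 and 19.4, so a difference of 5.4; SDs 3.2 and 5.3; two-sided 5%; 90% power; 44 evaluable and 56 enrolled per arm; post-baseline HAMA at days 14 and 28 and months 1 and 3.

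**Assumptions, not in the article.** Baseline to day-28 correlation ρ of 0.3 to 0.6; equal correlation between visits of 0.4 to 0.7; SD of within-patient change 4.5.

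**The plan's own figure.** Root-mean-square SD = √((3.2² + 5.3²)/2) = 4.38. Patients per arm = 2 × ((1.960 + 1.282) × 4.38/5.4)² = 13.8, so 14 (15 by t-test). The stated 44 per arm is not reproduced. That is a separate matter; 44 is used below because it is the planned evaluable number.

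**1. Baseline adjustment.** Difference detectable at 90% power, unadjusted raw scores: 3.2415 × 4.38 × √(2/44) = 3.03 points. ANCOVA multiplies the variance by 1 − ρ² and the detectable difference by √(1 − ρ²):

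| ρ | variance factor | detectable difference | power for a true 3 points |
|---|---|---|---|
| none | 1.00 | 3.03 | 89.5% |
| 0.3 | 0.91 | 2.89 | 92.1% |
| 0.5 | 0.75 | 2.62 | 96.0% |
| 0.6 | 0.64 | 2.42 | 98.0% |

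If change scores are analysed instead, and the SD is the same at both visits, their variance factor is 2(1 − ρ): 1.40, 1.00 and 0.80. ANCOVA is then (1 + ρ)/2 of that: 0.65, 0.75 and 0.80. So it gains precision under either definition of the outcome. At the planned 5.4 points the unadjusted raw-score test with 44 per arm already has power above 99.9%.

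**2. Several visits at 0.05.** Simulated chance of at least one false positive among equally correlated two-sided z-tests:

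| inter-visit correlation | days 14 and 28 | all four visits |
|---|---|---|
| 0.4 | 9.3% | about 16.5% |
| 0.5 | 9.1% | 15.5% |
| 0.7 | 8.3% | 13.0% |

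**3. Within-arm tests.** If each arm's test has power p and both arms truly change equally, exactly one is significant with probability 2p(1 − p). Here p comes from a paired t-test with 56 patients and standard error 4.5/√56 = 0.60:

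| true change in both arms | p | exactly one arm significant |
|---|---|---|
| 1.0 | 0.372 | 46.7% |
| 1.2 | 0.500 | 50.0% |
| 1.5 | 0.688 | 42.9% |
| 2.0 | 0.904 | 17.3% |
| 2.5 | 0.983 | 3.3% |
| 3.0 | 0.998 | 0.3% |

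**The case against.** Several stronger readings are tempting, and the article does not support them.

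- **That the ANOVA runs across visits, leaving no between-arm test.** Repeated scores have their own sentence. With two arms, the one-way ANOVA is most naturally the MA-versus-PA comparison, equivalent to a t-test. The plan has a between-arm test; what it lacks is a visit and a covariate.
- **That baseline is thrown away.** This is certain only for raw scores. If the outcome is change, as in the Background, baseline enters by subtraction, though without adjustment. Either way, an unadjusted comparison of randomised arms is unbiased, so the loss is one of precision.
- **That HAMA has four co-equal primary tests.** The primary-outcome section lists only days 1, 14 and 28; months 1 and 3 appear under follow-up, to see whether the effect lasts. On that reading there are at most two primary looks, and the after-treatment basis of the sample size points to day 28.
- **That within-arm tests will mislead about half the time.** That rate is the peak of 2p(1 − p), and it falls below 1% for a 3-point change. Nowhere does the article say that efficacy will be claimed by comparing within-arm p-values.

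An analysis plan that is not shown may name the visit, and the normality pre-test and reporting details can fairly be left to it. What stands is that the article does assign methods: unadjusted tests to the primary outcome and covariance analysis to the hormones. It also gives the primary outcome two definitions.

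**Conclusion.** The point holds as a free improvement, not as a flaw that invalidates the comparison. The stated between-arm HAMA test is unadjusted and attached to no visit, the repeated-measures or Friedman step reads as within-arm (Friedman has no group factor), and the two definitions of the primary outcome conflict.

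Naming one contrast matters most: it keeps the error rate at 5% instead of 8% to 9% with two primary visits, or roughly 13% to 16.5% if all four were so treated. Baseline adjustment is secondary: a modest gain at ρ = 0.3 and a substantial one at 0.6, of practical value only if the true effect is well below 5.4 points. All these sizes rest on assumed correlations; restricting entry to HAMA 14 to 28 tends to lower the baseline correlation. The within-arm discordance ranges from under 1% to 50% and shows only that such tests cannot stand in for the between-arm contrast.

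**What to change.** - State one primary test: the MA-minus-PA difference in HAMA at day 28, with 95% CI, from ANCOVA with baseline HAMA as covariate, at two-sided 0.05.
- Reconcile the Background and the HAMA score section to match. With baseline as covariate, the day-28 score and the change from baseline give the same treatment difference, so one sentence suffices.
- Name this one model. A mixed model is not interchangeable with it when patients drop out, because the two handle missing scores differently.
- Make the day-14 and month 1 and 3 contrasts secondary. For the latter, note that the Ancillary and post-trial care section gives PA patients MA sessions after treatment, so those contrasts may no longer compare MA with placebo alone. A model restricted to days 14 and 28 cannot supply them.
- Label the within-arm repeated-measures or Friedman tests as descriptive.

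**Cost.** Wording only. No extra patients, visits or measurements are needed, and covariance analysis is already planned for the hormones in the same software. The article reports enrolment as ongoing and the analysts as blinded, so the change can be fixed before allocation is revealed to them.

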**Methods:**

This study is a single-center, randomized, single-blind clinical trial that will be conducted in the First Affiliated Hospital of Guangzhou University of Chinese Medicine. A total of 112 eligible GAD patients will be randomly assigned (1:1) to receive MA (*n*=56) or PA (*n*=56) three times per week for 4 weeks. The primary outcome measure will be the HAMA score. The secondary outcome measures will be the GAD-7 and PSQI scores and the levels of CORT and ACTH. The evaluation will be executed at baseline, 2 weeks, the end of the treatment, and a follow-up 3-month period. All main analyses will be carried out based on the intention-to-treat (ITT) principle.

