#### CORT and ACTH

It has been suggested that anxious subjects demonstrate greater CORT and ACTH concentrations [28]. In this study, we will draw serum samples and investigate CORT and ACTH before and after acupuncture. An enzyme-linked immunosorbent assay (ELISA) will be used to measure CORT and ACTH. These related tests will be carried out by the clinical laboratory of the First Affiliated Hospital of Guangzhou University of Chinese Medicine.

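### CORT and ACTH are analysed by covariance analysis or by an unadjusted rank test depending on an unidentified F-test; on one plain reading this gate is inverted and costs power

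*Protocol article*

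**What the plan says.** CORT and ACTH are secondary outcomes. The abstract lists them: "The secondary outcome measures will be the GAD-7 and PSQI scores and the levels of CORT and ACTH". The section on CORT and ACTH gives the sampling: "we will draw serum samples and investigate CORT and ACTH before and after acupuncture".

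The section Data monitoring and analysis sets the rule for these two outcomes. If the significance of an F-test "of the univariate linear model is greater than 0.05, CORT and ACTH will be subjected to covariance analysis". The alternative follows: "If not, the Kruskal-Wallis rank sum test will be performed". The same section fixes the test level: "All statistical tests will be two-sided, and the significance level will be set at 0.05".

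The rule does not say which F-test is meant, which covariate enters the covariance analysis, or whether the rank test is run on post-treatment values or on changes. The two rules before it, for HAMA, GAD-7 and PSQI, are gated on a normality test. This one is not.

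**The concern.** The protocol states a decision rule here, so this is not a detail left to an unseen analysis plan. The rule has three weaknesses.

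- **It depends on the data.** The method is chosen from a significance test on the same trial data that the method will analyse.
- **It is undefined.** Two analysts could follow the sentence faithfully and run different analyses, and CORT and ACTH could end up under different methods.
- **Its fallback is weak.** Kruskal-Wallis drops whatever covariate was to be used. It does not deal with unequal slopes, and it gives no adjusted effect estimate.

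Taken as the test of the model as a whole, the direction is also backwards. A small p-value means that the model explains the outcome, and that is when adjustment helps most. At stake are power and clarity for the outcomes through which the trial explores a mechanism via the HPA axis.

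**Working it through.** **Inputs from the protocol.** 56 enrolled and 44 evaluable per arm ("we set the sample size of 44 patients in each group"), 1:1 allocation, two-sided 0.05. The protocol states no power, effect size or correlation for CORT or ACTH, so it has no figure of its own to reproduce on this point. Its sample size calculation concerns HAMA only. The main figures use 56 per arm because dropouts are to be analysed with their last available value; 44 is shown as a check.

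**Assumptions.** Baseline is the covariate (inferred from the before-and-after sampling). Baseline-to-post correlation ρ is 0.3, 0.5 or 0.7. The true effect is 0 or d = 0.5 SD. Data are normal with equal slopes. Kruskal-Wallis is run on post-treatment values unless stated.

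**Step 1: power of the two branches, by formula.** With Φ the standard normal distribution function:

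- ANCOVA: Φ(d·√(n/2) / √(1−ρ²) − 1.96)
- Kruskal-Wallis on post values: Φ(d·√(n/2)·√(3/π) − 1.96)
- Kruskal-Wallis on changes: Φ(d·√(n/2)·√(3/π) / √(2(1−ρ)) − 1.96)

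For n = 56, d·√(n/2) = 0.5 × √28 = 2.646, and 2.646 × √(3/π) = 2.585.

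| ρ | ANCOVA | K-W, post values | K-W, changes |
|---|---|---|---|
| 0.3 | Φ(2.774 − 1.96) = 79% | Φ(2.585 − 1.96) = 73% | Φ(2.185 − 1.96) = 59% |
| 0.5 | Φ(3.055 − 1.96) = 86% | 73% | Φ(2.585 − 1.96) = 73% |
| 0.7 | Φ(3.705 − 1.96) = 96% | 73% | Φ(3.338 − 1.96) = 92% |

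Simulation with 4,000 trials per setting agrees: ANCOVA 85% and 95% at ρ = 0.5 and 0.7; Kruskal-Wallis on post values about 73% and 71-73%; on changes 57%, 73% and 91% at the three correlations.

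**Step 2: which branch each reading selects.** Simulation, 44 per arm, effect 0.5 SD:

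| F-test read as | ANCOVA reached, ρ = 0.3 / 0.5 / 0.7 | Power of the rule | Power of ANCOVA always |
|---|---|---|---|
| Overall model | 7.3% / 0.1% / 0% | 62 / 62 / 62% | 68 / 75 / 90% |
| Arm | 32% / 25% / 10% | 59 / 59 / 60% | same |
| Slope homogeneity | about 95% | 67 / 74 / 89% | same |
| Levene | about 95% | 67 / 74 / 88% | same |

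Under the overall-model reading the rule is in effect the rank test. At 56 per arm it therefore loses about 85 − 73 = 12 points at ρ = 0.5 and 22 to 24 points at ρ = 0.7 (95 − 73 or 95 − 71). At ρ = 0.3 the loss is about 79 − 73 = 6 points.

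Under the arm reading, covariance analysis is kept only when its own arm test is not significant. The rule can then declare a difference only when both the arm test and Kruskal-Wallis reject, which makes it conservative.

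**Step 3: type I error.** Simulation with no effect, 44 per arm: overall-model reading 4.5-4.8%; arm reading 3.2%, 2.8% and 1.5% at ρ = 0.3, 0.5 and 0.7; slope and Levene readings 4.6-5.9%. The 5.9% equals the figure for ungated ANCOVA in the same run. The Monte Carlo standard error is √(0.05 × 0.95 / 4000) = 0.34 points.

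**The case against.** The strongest reply is that the benign reading fits its surroundings. The neighbouring rules have the form of an assumption check: if it is met, use the parametric method; if not, use ranks. A slope-homogeneity or Levene test with p above 0.05 leading to covariance analysis is the conventional direction, and the loss is then at most about 2 points. This stands. A reader might infer that the plan as written throws away baseline adjustment just when it matters most. The text does not support that as a fact, because it never says that the F-test is the overall one.

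Three further points also stand:

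- The largest loss assumes a rank test on post-treatment values. The Discussion speaks of evaluating changes, and on change scores the loss at correlation 0.7 shrinks to about 4 points (91% against 95%). Nothing is recovered at 0.5, and at 0.3 change scores do worse (57%).
- A reader might infer a false-positive risk from a data-driven gate. The figures show none of any size; the one clear effect is conservatism under the arm reading.
- The outcomes are secondary and the mechanism aim is exploratory.

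The objection does not rescue the rule. If an assumption check was meant, the sentence does not say so, and the fallback does not suit it: an unadjusted rank test does not address unequal slopes and still discards the baseline.

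**Conclusion.** The point holds in a conditional form. The protocol fixes a data-dependent and undefined gate whose fallback uses no covariate, and no reading examined gives the gate a material advantage over simply adjusting for baseline. The cost depends on the F-test meant:

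- **Overall model:** inverted. About 12 points of power are lost at correlation 0.5, 22 to 24 at 0.7 (about 4 there with change scores), and about 6 at 0.3.
- **Arm:** conservative, with type I error about 2-3%.
- **Slope homogeneity or Levene:** conventional in direction, at most about 2 points lost, poor fallback.

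These figures rest on an assumed 0.5 SD effect, assumed correlations, normal data and an inferred baseline covariate; none is given in the protocol. Truly unequal slopes were not simulated. The primary HAMA analysis is not affected.

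**What to change.** Delete the F-test gate. State that post-treatment CORT and ACTH will each be analysed by ANCOVA with arm and the baseline value of the same hormone in all cases, on the log scale if skew is expected, with that choice made in advance. Report the adjusted difference, or the ratio on the log scale, with a 95% CI. A rank-based ANCOVA may be added as a sensitivity analysis.

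If the authors prefer to keep a check, they should at least name the F-test and the covariate and choose a fallback that retains the baseline.

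The cost is two sentences of analysis wording. No visit, sample or data item changes. The change should be recorded before hormone results are seen by arm.

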### Quality control

Two independent study assistants will input the data to avoid mistyping. Before the beginning of the trial, all intervenors will be trained, and another assistant will follow the intervention procedures and stay in the outpatient department to ensure consistency of acupuncture intervention among intervenors. In addition, quality inspectors will check the CRFs randomly to ensure that there are no recorded errors.

## Discussion

According to recent meta-analyses or systematic reviews [29, 30], acupuncture shows to have a better treatment efficacy for GAD, but the conclusions are limited. Many articles have compared efficacy between MA and PA, but the conclusions are different. Some reviews [31–34] have concluded that MA is definitely better than PA, and other reviews [35] found no difference between MA and PA. The jury is out on whether or not there is an existing acupuncture placebo effect. To the best of our knowledge, no trial has studied the efficacy of MA versus CBT in treating GAD. In the present research [36], CBT combined with electroacupuncture (EA) resulted in a lower HAMA score than CBT or EA alone. In China, CBT is not as widespread as in Western countries. The expense of CBT is much higher than that of acupuncture, so a few GAD patients will choose CBT to treat GAD. Therefore, this trial compared MA and PA to determine whether there is a placebo effect and provide clinical evidence of the placebo effect of acupuncture.

There are many types of anxiety disorders and GAD is one of the most common types. The HAMA, introduced in 1959, was widely used in evaluating anxiety levels in lots of clinical trials. The GAD-7, introduced in 2006, was designed for GAD; this is a special type of anxiety disorder. However, RCTs about anxiety used GAD-7 as an outcome are limited. Due to the specificity of the GAD-7 and the generalization of the HAMA, we will use the HAMA scores as the primary outcome and the GAD-7 scores as the secondary outcome to measure the change in patients’ anxiety levels. We will use the PSQI scores as a secondary outcome because there is a high rate of comorbidity between insomnia and GAD [37, 38]. Less sleeping will aggravate patients’ mental burden and worsen their anxiety. Therefore, we want to determine whether there is a connection between GAD and sleeping. In addition, we will collect serum samples of GAD patients to evaluate the changes in CORT and ACTH during treatment. If the levels of CORT and ACTH are associated with the level of GAD, acupuncture may treat GAD via the HPA axis.

This study has room for improvement. First, due to the nature of acupuncture, we spare no effort to maintain blinding, but we still cannot find a perfect way to achieve double blinding. We can make the pedestal of acupuncture needles that look the same and simulate the feeling of being needled by touching with semi blunt needles. Therefore, patients are unaware of whether they receive MA or PA. However, experienced acupuncturists can feel the difference in whether needles prick the skin and achieve Deqi or not. Second, this study is a single-center trial, and we hope that this study will provide more clinical evidence and design a multi-center trial to confirm the efficacy of acupuncture in treating GAD.

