## Abstract

**Background:**

Generalized anxiety disorder (GAD) is common among perimenopausal women. Acupuncture may be an effective treatment for GAD, but evidence is limited. The pathogenesis of GAD is not yet clear, but it is related to the hypothalamic-pituitary-adrenal axis and its excretion, cortisol (CORT), and adrenocorticotropic hormone (ACTH). The object of this study is to evaluate the efficacy of manual acupuncture (MA) versus placebo acupuncture (PA) for perimenopausal women with GAD.

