### Inclusion criteria

Patients who meet all of the following criteria will be allowed to enrollment:
Aged 45 to 55 years old (female only).Meet the diagnostic criteria of DSM-5 [1] for GAD.Excessive anxiety and worry (apprehensive expectation), occurring more days than not for at least 6 months.The individual finds it difficult to control the worry.The anxiety and worry are associated with three (or more) of the following six symptoms (with at least some symptoms having been present for more days than not for the past 6 months):Restlessness or feeling keyed up or on edge.Being easily fatigued.Difficulty concentrating or mind going blank.Irritability.Muscle tension.Sleep disturbance (difficulty falling or staying asleep, or restless, unsatisfying sleep).(4)The anxiety, worry, or physical symptoms cause clinically significant distress or impairment in social, occupational, or other important areas of functioning.(5)The disturbance is not attributable to the physiological effects of a substance (e.g., a drug of abuse, a medication) or another medical condition (e.g., hyperthyroidism).(6)The disturbance is not better explained by another mental disorder (e.g., anxiety or worry about having panic attacks in panic disorder).(7)The score of HAMA is between 14 and 28.(8)No anti-anxiety drugs or other psychotropic drugs in the last 2 weeks.(9)No participation in any other research in the last 1 month.

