### Placebo acupuncture (PA) group

Patients in the PA group will receive placebo acupuncture in which the needles will not be inserted into the skin and will not induce the Deqi sensation. The blunt-tipped placebo needle (φ0.30 × 40 mm, produced by Huanqiu Co. Ltd., China) can provide participant-blinding effects with a similar appearance to conventional needles but no skin penetration.

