### Ancillary and post-trial care

After the whole treatment, patients who received PA treatment will receive 12 sessions of MA treatment to compensate. If patients who receive MA treatment want to continue treatment, they can appoint and be treated in the outpatient department.

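### The Discussion says the trial will show whether acupuncture has a placebo effect, but a comparison of manual with placebo acupuncture, with no untreated arm, cannot show this

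*Protocol article*

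**What the plan says.** The abstract (Methods) describes two arms only: participants "will be randomly assigned (1:1) to receive MA (*n*=56) or PA (*n*=56) three times per week for 4 weeks". The Sample size section gives the same two groups, and Study design mentions no third. PA uses the same acupoints as MA, but "the needles will not be inserted into the skin and will not induce the Deqi sensation".

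The formal purpose is stated in the abstract (Background): "The object of this study is to evaluate the efficacy of manual acupuncture (MA) versus placebo acupuncture (PA) for perimenopausal women with GAD". The abstract's Discussion and the last paragraph of the Background section say the same in other words.

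The main Discussion states a different target. After noting that reviews disagree on whether MA is better than PA, it says "The jury is out on whether or not there is an existing acupuncture placebo effect", and closes the paragraph by saying that "this trial compared MA and PA to determine whether there is a placebo effect and provide clinical evidence of the placebo effect of acupuncture".

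Two other places bear on how that claim might be pursued. Data monitoring and analysis, besides the between-group tests, plans an analysis over time: "The repeatedly assessed HAMA, GAD-7, and PSQI scores in the MA or PA group will be subjected to a normality test", followed by repeated-measures analysis of variance or the Friedman test. Inclusion criteria select patients on the primary outcome scale: "The score of HAMA is between 14 and 28".

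**The concern.** To learn whether sham needling has a placebo effect, patients who receive the sham must be compared with similar patients who receive no needling. This trial has no such group. What it compares is real needling with sham needling, and the placebo response is common to both.

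The stake is the conclusion that readers are told to expect. The article itself reports that earlier reviews disagree on MA versus PA, so a null result is a real possibility. Under the sentence in the Discussion, a null result could be taken as evidence that acupuncture works through placebo, although it would be just as compatible with no placebo effect at all. The limitations paragraph of the Discussion covers blinding and the single centre, but not this.

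**Working it through.** The article gives no figure, estimand, comparator or decision rule for a placebo effect, so there is no planned number to reproduce. The check is whether the design can identify the quantity named.

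**Step 1: what each arm contains.** Let N be the mean improvement from natural course and regression to the mean, P the placebo response to the procedure, and S the added effect of penetration and Deqi. With common mean baseline B and additive effects:

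- mean PA score = B − N − P
- mean MA score = B − N − P − S
- PA − MA = S

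P does not appear in the contrast. If S = 0, the contrast is 0 for every P.

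**Step 2: the same with numbers.** The Sample size section gives post-treatment HAMA means of 14.0 (MA) and 19.4 (PA), so S = 19.4 − 14.0 = 5.4. The article gives no mean baseline. Assume B = 24.8, which lies inside the entry window. The fall in PA is then N + P = 24.8 − 19.4 = 5.4 (equal to S only because of the baseline chosen).

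| P | N | PA mean | MA mean | PA − MA |
|---|---|---|---|---|
| 0 | 5.4 | 19.4 | 14.0 | 5.4 |
| 2 | 3.4 | 19.4 | 14.0 | 5.4 |
| 5.4 | 0 | 19.4 | 14.0 | 5.4 |

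A placebo effect of zero and one that accounts for the whole fall in PA give identical arm means and an identical contrast. No sample size can tell them apart.

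**Step 3: the change within PA.** This is the only other quantity available, and it estimates N + P. Part of N may be regression to the mean, because entry requires HAMA 14 to 28 and HAMA is also the outcome. This applies where the qualifying score also serves as the baseline.

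The possible size can only be illustrated, since every input is assumed: a normally distributed screened population with mean 14 to 18 and SD 5 to 6, test–retest correlation r of 0.6 to 0.8, entry truncated at 13.5 and 28.5, and P = S = 0. The expected fall is (1 − r) × (mean after truncation − population mean). Power is for a paired t-test with 56 patients at two-sided 5%.

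- Mean 18, SD 5, r 0.8: 0.2 × (19.39 − 18) = 0.28 points; significant about 10% of the time.
- Mean 16, SD 6, r 0.7: 0.3 × (18.99 − 16) = 0.90 points; about 32%.
- Mean 14, SD 6, r 0.6: 0.4 × (18.30 − 14) = 1.72 points; about 72%.

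So PA could fall by roughly 0.3 to 1.7 points with no placebo effect, before any natural improvement. The article plans repeated-measures analysis of variance or Friedman, so these percentages do not describe its own tests.

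**Step 4: follow-up.** Ancillary and post-trial care says that "patients who received PA treatment will receive 12 sessions of MA treatment to compensate", and Follow-up plans scores in the first and third months after treatment. If the compensating sessions fall before those assessments, later PA scores also contain an MA effect and say still less about placebo.

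**The case against.** The strongest reply is that the sentence is rationale in a Discussion and is not the objective. Every formal statement of purpose concerns efficacy of MA versus PA, which the design identifies. This stands, and it limits the point to interpretation.

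A second reply is that the sentence, read after the remark on conflicting reviews, means only to ask whether acupuncture's benefit goes beyond placebo. That question fits the design, and loose wording is a plausible explanation. But the text names the existence of a placebo effect as the open question and promises clinical evidence of that effect. Even on the generous reading, a null contrast would not show that a placebo effect exists.

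A reader might also infer that the within-group tests are planned as the evidence for a placebo effect. The article does not support this: Data monitoring and analysis lists those tests without tying them to any placebo claim. They are a route by which the error could arise, not a planned inference. Nor should the regression-to-the-mean figures be read as the size of harm in this trial, because screened mean, SD and correlation are all absent from the article and the range reflects the values chosen.

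Finally, a reader might infer that the trial needs an untreated arm or that its main comparison is compromised. Neither follows, since the stated efficacy objective does not depend on P.

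**Conclusion.** The point holds as a minor one of interpretation. The Discussion promises a conclusion about a placebo effect that neither the MA–PA contrast nor the within-PA change can supply. The placebo effect is not identified: any size from zero upwards fits any MA–PA result. The additive model is used to show this simply, but the underlying reason is the lack of a group without needling. The conclusion does not rest on the assumed baseline or on the assumed regression-to-the-mean inputs, which are illustration only. The formal objective and the primary comparison are unaffected.

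**What to change.** In the Discussion, replace the sentence with one saying that the trial compares MA and PA to determine whether MA reduces HAMA more than PA. Add that neither a non-significant MA–PA difference nor the change over time within PA will be interpreted as evidence of a placebo effect, because there is no untreated arm and the within-PA change also contains natural course and possible regression to the mean.

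The cost is wording in the protocol and the eventual report. No patient, visit, endpoint or analysis changes. The small downside is giving up a claim that the design cannot support.
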